### Treatments

#### Structure

The treatment in both conditions is a multicomponent inpatient program, components including a combination of small groups, individual, and milieu therapy lasting for 13 consecutive weeks, with two of these weeks the patients have a home stay where they practice new behavior. The treatment is closed, that is the patients start and end treatment at the same time and the group is not open to new patients if others end treatment. There are six group therapy sessions each week, altogether 66 group sessions. The duration of group session is 90 min. There are three individual therapy sessions each week, two of them with the individual therapist, and one with the milieu therapist, altogether 33 individual session. The duration of the individual session is 55 min. In these group and the individual sessions, the therapists deliver specific CBT or CFT treatment delivered in accordance with the respective treatment protocols, the manuals for which are available upon request from the first author. In addition to the specific therapy, both groups will participate in physical activity for 90 min and a community group meeting for 60 min each week.

#### Common Content

Both conditions have a focus on the working alliance in which therapist and the patient collaborate to overcome the ED. Underweight patients are encouraged to be active and responsible during the process of weight regain and weight maintenance. If these patients feel controlled it tends to increase their resistance. Both conditions are in addition designed to replace dysfunctional eating patterns with normal eating habits, and develop strategies for resisting binging and purging. The patients have to eat sufficient food to meet the body’s demands for energy. Ongoing self-monitoring and the accomplishment of planned homework assignment at the hospital are of importance to achieve and maintain the change.

#### Specific Content of Cognitive Behavioral Therapy (CBT)

The cognitive behavioral therapy treatment used in this trial is an adaptation of outpatient CBT for ED, postulated by Waller et al. (2007). It uses the same procedures and strategies but it is more intensive. It is primarily concerned with the processes that are maintaining the patients’ ED psychopathology, with cognitive processes being viewed of central importance. It uses cognitive, behavioral, and psychoeducational strategies. The treatment is suitable for all forms of ED diagnosis, as long as inpatient management is appropriate. The specific ED diagnosis is not of relevance to the treatment. It is the defined problems present and the processes that appear to be maintaining them that guide the content of the treatment. The key strategy of CBT is to create a case formulation of the maintaining mechanisms of the patients’ psychopathology. The formulation is used to identify the features to address in the treatment. An initial personal formulation is built with patients in the beginning of the treatment, but is revised during the treatment if necessary. If the patients have trauma symptoms that maintain their ED, and the patients do imaginal exposure and/or imagery rescripting. The treatment is designed to reduce ED symptoms and enhance their control over life but is also concerned with the entire psychosocial functioning of the patients (see Table 1).

**Table 1 T1:** Differences in approach and interventions used in cognitive-behavioral therapy and compassion-focused therapy.

Approach used	CBT	CFT
Psychoeducational interventions	• Educate about the nature of CBT • Anxiety management training, relaxation, and distraction techniques	• Educate about the nature of CFT • Mindfulness – learning how to pay attention in the present moment • Understanding symptoms (e.g., restricting or binging) as related to safety and emotion regulation strategies • Understanding the origins and functions of self-criticism, shame, and pride • Learning to observe self with self-kindness and warmth
In-session work	• Socratic questions, focus toward overevaluation of eating, shape and weight, and schema level beliefs • Cognitive restructuring to examine core beliefs, dysfunctional assumptions, and negative automatic thoughts • Challenging maintaining behaviors and physical states • If trauma symptoms maintain ED; imaginal exposure of trauma scenes	• Developing compassionate focus using a variety of interventions, including compassionate imagery, thinking, behavior, or emotion • Working on the fears and blocks to developing compassion • Socratic questions, focus toward self-critical thoughts • Compassionate letter writing – focusing on being kind, supportive, and nurturing Develop sensitivity and acceptance into one’s own difficulties through self-reflection
Behavioral experiments	• Use of exposure therapy, meal planning • Exposure and making predictions toward meals, weight, and shape	• Exposure toward meals, weight, and shape with focus toward exploring what the compassionate self could say/do in the situation to help
Self-monitoring	• Completion of thought records, charts, cost benefit analysis to explore emotions thoughts, behavior, and bodily reactions	• Examining positives, e.g., what went well, and focusing on specific qualities • Use of self-compassion diary

**Table 2 T2:** Method and timing of assessment.

Measure	Initial assessment	Start of treatment	During treatment	End of treatment	Follow-up
Sociodemographic data	×	×		×	×
MINI	×				×
EDI-I	×	×		×	×
CTQ	×				
EDE-Q	×	×	×	×	×
SCL-90R	×	×		×	×
EDI-2	×	×		×	×
IIP	×	×		×	×
BDI	×	×		×	×
SF-36	×	×		×	×
PSS-SR	×	×	×	×	×
WAI			×		
SCS	×	×	×	×	×
ATQ			×		

*EDE-I, eating disorder examination interview; MINI, mini international neuropsychiatric Interview; CTQ, childhood traumatic questionnaire; SCL-90R, symptom check list 90 revised; EDE-Q, eating disorder examination questionnaire; EDI, eating disorder inventory; IIP, inventory of interpersonal problems; BDI, beck depression inventory; SF-36, short form health survey; PSS-SR, post traumatic symptom scale self-rating; WAI, working alliance inventory; SCS, self-compassion scale; SCL-5; symptom checklist-5; ATQ, automatic thought questionnaire; HRV; heart rate variability.*

#### Specific Content of Compassion-Focused Therapy (CFT)

The compassion-focused therapy treatment used in this trial is an adaptation of outpatient CFT for ED, postulated by Gale et al. (2014) and Goss and Allan (2014). It uses the same procedures and strategies but it is more intensive. CFT offers a structured approach to help patients gain control of their chaotic eating patterns, trauma symptoms (for trauma patients), and the processes that underlie them. It is primarily concerned with the processes of developing a compassionate approach to managing the physical and emotional demands of following a structured eating program and to reduce shame, in particular body shame.

To increase compassion and reduce shame, compassionate mind training (CMT) is a central part of the program. CMT has two main aims, the first is to help patients develop their soothing system, and use this to regulate other motivational systems and affective states (e.g., feat, anger, or disgust). The second is to use a range of techniques and group work to help patients develop a compassionate motivational system and develop their capacities of giving compassion to others, receiving compassion from others, and for self-compassion. It is especially focused on helping the patients imagine a future in which they can be motivated by compassion and no longer need their ED. It also helps to identify and work with blocks to feeling safe and experiencing compassion from others and compassion for the self. Because their “compassion” systems are so under-used and unfamiliar they often find this very challenging, particularly if their self-identity, and sense of pride has been linked to their ED. CMT uses imagery tasks that are designed to give space to experience and practice generating specific types of motivations and emotions associated with compassion.

One of the key foci of these exercises is to help the patient develop a more compassionate relationship with themselves. Within the treatment program, this is specifically targeted at managing ED symptoms, the issues that trigger them, and the functions they serve. Thus, we would explore questions such as “How would a compassionate person help you to eat?” or “What compassionate things could you do or say to help you eat breakfast?” The key is to develop coping thoughts and response that are “felt” to be helpful, to enable patients to let go of ED behaviors that have come to feel “safe” ways of managing difficult emotions or experiences and to develop more “self-caring” behaviors in everyday life (see Table 1).

### Screening Instrument and Primary Treatment Outcome

The trial uses standardized instruments with good psychometric properties and high clinical utility. Demographic variables (age, sex, social conditions, education, and connection to the labor market), previous treatment, medication, BMI, and pregnancy are assessed at the first assessment interview with a psychologist and by a psychiatrist or attending physician at their assessment interview (part of the clinical routine) (see Table 2).

#### Mini International Neuropsychiatric Interview (MINI) (Sheehan et al., 1998)

Mini international neuropsychiatric interview is used to assess present psychosis, depression, suicidal risk and abuse of alcohol, medicine and/or narcotics. MINI is a short structured diagnostic interview compatible with international diagnostic criteria, including the international classification of diseases (ICD-10) and the Diagnostic and Statistical Manual of Mental Disorders (DSM-IV).

#### Eating Disorder Examination – Interview (EDE) (Fairburn et al., 2008)

Eating disorder examination will be used in order both to obtain ED diagnosis for inclusion and as a treatment outcome measuring at discharge and 12-months follow-up. We use the authorized Norwegian version (version 12 and 17). These interviews are performed by four interviewers trained by an experienced clinician and researcher. The assessors are blind to the patients’ treatment condition and have no involvement with treatment. Two primary outcome variables will be generated from the EDE ratings: change in the severity of ED features as measured by the global EDE score, and having a global EDE score less than one standard deviation above the community mean (i.e., below 1.74) (Kendall et al., 1999). Normative comparisons of this type are widely used to identify clinically significant change (Kendall et al., 1999; Ogles et al., 2001; Kazdin, 2003).

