### Objective

The first objective of this study is to assess the relative effects CBT and CFT in terms of recovery from ED defined as change from baseline to post-treatment in the global score of EDE. The mean scores in the two intervention groups are compared. The second objective is to assess whether – for patients with trauma compared to those without – CFT is more effective in (i) reducing ED psychopathology, (ii) reducing general symptoms and trauma symptoms, and (iii) improving health-related quality of life. The third objective is to examine the process of therapy by assessing self-compassion, cognitions, and alliance repeatedly over the course of treatment to examine their possible predictive and mediating effects on treatment outcome.

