### Power Estimation

A lower-bound probability of detecting effects in clinical research (power) of 0.80 has been suggested (Cohen, 1988). To get some idea of the statistical power in the present study, we estimated the necessary number of observations (*n*) for achieving a power of 0.80 of detecting a medium effect (Cohen’s *d* = 0.5) using an alpha level of 0.05 for three common tests: Calculations of statistical power were performed with G^∗^Power (Buchner and Erdfelder, 1996). All other statistical analyses were conducted with SPSS.

The primary outcomes in the two groups were compared using analysis of covariance (ANCOVA) with pre-treatment values as the covariate. Making the conventional assumptions of no treatment by pre-treatment interaction, this may be formulated as:

(1)$${\text{Post}}_{\text{i}}=\alpha +\beta_{1}^{*}{\text{Treatment}}_{\text{i}}+\beta_{2}^{*}{\text{Pre}}_{i}+\varepsilon_{\text{i}}$$

The treatment-effect may be estimated by the increase in explained variance when including the Treatment effect in the model. Using *d* = 0.5 this corresponds to an increase in *R*^2^ of 0.06. Assuming a rejection criterion (alpha) of 0.05 and a desired power of 0.80 of detecting an increase in *R*^2^ of 0.06, the estimated required sample size is 62 patients per treatment condition.

The design also included a dichotomous “trauma” condition (see section “Introduction”). Reasoning as above the model may be formulated as:

(2)$${\text{Post}}_{\text{i}}=\alpha +\beta_{1}^{*}{\text{Treatment}}_{\text{i}}+\beta_{2}^{*}{\text{Trauma}}_{\text{i}}+\beta_{3}^{*}{\text{(Treatment}}_{\text{i}}^{*}{\text{Trauma}}_{\text{i}}\text{)}+\beta_{4}^{*}{\text{Pre}}_{i}+\varepsilon_{\text{i}}$$

The effect of interest, the Treatment by Trauma interaction, will be estimated by the increase in explained variance when including this effect in the model over a model with all other effects included. Assuming a rejection criterion (alpha) of 0.05 and a desired power of 0.80 of detecting an increase in *R*^2^ of 0.06, the estimated required sample size is 64 patients per treatment condition. The statistical power of the present study with total *N* = 144 thus appears adequate.

As there seems to be no single standard for power analysis within disaggregating between patient effects from the effect of individual patients using longitudinal mixed models, we did not conduct further power, or sample size for this analysis.

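### Two primary outcomes are named, one of them yes/no, but the objective, the stated ANCOVA and the claim that N = 144 is adequate cover only the continuous EDE score

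*Protocol article*

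**What the plan says.** All references are to the protocol article; no separate analysis plan is at hand.

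- **Eating Disorder Examination – Interview.** "Two primary outcome variables will be generated from the EDE ratings". The first is "change in the severity of ED features as measured by the global EDE score"; the second is "having a global EDE score less than one standard deviation above the community mean (i.e., below 1.74"). The Abstract names the same two. The interview is used "as a treatment outcome measuring at discharge and 12-months follow-up".
- **Objective.** The first objective concerns "recovery from ED defined as change from baseline to post-treatment in the global score of EDE", compared as group means. The below-1.74 status is absent, although the word recovery is attached to the mean change.
- **Power Estimation.** "The primary outcomes in the two groups were compared using analysis of covariance (ANCOVA) with pre-treatment values as the covariate". The equation shown regresses a post score on treatment and pre score. The calculations take d = 0.5 (R² increase 0.06), power 0.80, "using an alpha level of 0.05 for three common tests". Two calculations follow: 62 per arm for the treatment effect and 64 per arm for treatment by trauma. Power at N = 144 is then called adequate.
- **Statistical Methods.** Treatment differences are to be analysed by hierarchical linear modelling (HLM), with no outcome named. The chi-square test mentioned is for baseline comparisons.

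**The concern.** These sections do not describe the same primary analysis. One sets two primary outcomes, another carries one, and a third gives both a model that fits only one. A linear model with normal errors is not a natural choice for a yes/no status. Using pre-treatment status as its covariate would also adjust for very little if few inpatients start below 1.74. That is an assumption, since no baseline EDE distribution is given.

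Two things are at stake. The recovery endpoint sits at primary rank in a trial described as adequately powered, with no recovery rate or power given for it. And because no rule says whether one or both outcomes must succeed, the trial's overall error rate and power cannot be read from the text.

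**Working it through.** **Inputs from the article.** d = 0.5, R² increase 0.06, alpha 0.05, target power 0.80, N = 144 with 1:1 allocation (144/2 = 72 per arm), cut-off 1.74. **Assumed, because not given:** recovery rates, a normally distributed score, and the pre-post correlation.

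**1. The article's own figure.** For an R² increase with one numerator df, f² = 0.06/(1 − 0.06) = 0.0638 and the noncentrality is λ = f²·N.

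- N = 124 (62 per arm): λ = 7.91, power 0.797.
- N = 125: power 0.800. The stated 62 per arm reproduces.
- Interaction: with the unrounded R² of 0.0588, the F test needs 128 in total, which is the stated 64 per arm.
- N = 144: λ = 9.19, power 0.853 for the treatment effect.

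**2. The yes/no outcome under the same shift.** If one arm recovers at rate p₁, a 0.5 SD shift gives p₂ = Φ(Φ⁻¹(p₁) + 0.5). For a pooled two-proportion test with n per arm and p̄ = (p₁ + p₂)/2:

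power = Φ[(|p₂ − p₁| − 1.96·s₀)/s₁], where s₀ = √(2p̄(1 − p̄)/n) and s₁ = √((p₁(1 − p₁) + p₂(1 − p₂))/n).

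For p₁ = 0.40 and n = 72: p₂ = 0.597, s₀ = 0.0833, s₁ = 0.0817, so power = Φ[(0.197 − 0.163)/0.0817] = 0.66.

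| p₁ | p₂ | Power, 72 per arm | n per arm for 0.80 |
|---|---|---|---|
| 0.20 | 0.366 | 0.60 | 115 |
| 0.30 | 0.490 | 0.65 | 103 |
| 0.40 | 0.597 | 0.66 | 100 |
| 0.50 | 0.691 | 0.65 | 102 |
| 0.60 | 0.774 | 0.62 | 110 |

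**3. The same outcome with baseline adjustment.** I simulated logistic regression on treatment, continuous baseline score and trauma stratum, with 72 per arm, about 40% v 60% recovery and 3,000 runs per setting. Power was 0.66, 0.68 and 0.73 for pre-post correlations of 0, 0.3 and 0.5. The simulation error is about 0.01, so roughly 0.65 to 0.75 is a fair statement.

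**4. What each decision rule would imply.** The correlation between a normal score and its own dichotomy at rate p is φ(z_p)/√(p(1 − p)), where z_p = Φ⁻¹(p). This is 0.70 at 20% and 0.80 at 50%.

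- *Either outcome at 0.05 suffices:* familywise error = 1 − P(|Z₁| < 1.96, |Z₂| < 1.96). This is 0.0781 at correlation 0.8 and 0.0835 at 0.7.
- *Both must succeed:* error stays at or below 0.05, but joint power cannot exceed the yes/no test's own power, about 0.60 to 0.66 unadjusted.
- *Alpha split 0.025/0.025:* power for the continuous score at N = 144 falls to 0.777, and 152 patients would be needed for 0.80.

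**The case against.** The strongest reply is that this is a condensed article. An alpha split or testing order is commonly left to the analysis plan, so its absence is no defect. That stands, and the point does not rest on it. It rests on what the article states: two primaries, an objective with one of them, a linear model given to both, and an adequacy claim derived for one.

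A second reply is that the ANCOVA sentence sits under Power Estimation and may only motivate the sample size, with HLM as the real analysis. That is a possible reading, but HLM as named is also a linear model, so the yes/no outcome still has none that suits it. The reply also exposes a further ambiguity: two candidate analyses for the continuous score.

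Three stronger readings are tempting, and the article does not support them:

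- *Each outcome is tested at 0.05 and either can declare success.* The 0.05 appears only as a power input, and no test of the yes/no outcome or success rule is described. The 8% is therefore conditional.
- *The stated error rate and power are wrong.* No familywise rate is stated, no power is claimed for the yes/no outcome, and the figures given for the continuous score reproduce.
- *Four primary tests, because the EDE is taken at discharge and at 12 months.* That is a measurement schedule. The first objective fixes the comparison at post-treatment.

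**Conclusion.** The point holds as an inconsistency in stated text, and it should be fixed. The sample size is right for the continuous EDE score, with power of about 0.85 at N = 144. The statement that N = 144 is adequate has no support for the second primary outcome. There, unadjusted power is about 0.60 to 0.66, given a 0.5 SD shift in a normal score and 20% to 60% recovery in one arm. Baseline adjustment could raise it to roughly 0.65 to 0.75 near 40% v 60% recovery, for a pre-post correlation of 0 to 0.5, which is still below 0.80. Familywise error of about 8% follows only under an either-outcome rule, which the article neither adopts nor excludes.

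**What to change.** 1. Make EDE global score at discharge the single primary outcome, in line with Objective and Power Estimation, and align the Abstract and the EDE section with it.
2. State whether ANCOVA or HLM is its primary analysis.
3. Make EDE global below 1.74 at discharge a key secondary outcome, tested only if the primary is significant. Use logistic regression on treatment, continuous baseline EDE global and trauma stratum.
4. Limit the adequacy statement to the continuous score. Report the power of the yes/no test with its assumptions, keeping the unadjusted and baseline-adjusted ranges apart so that the figure describes the test actually planned.

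Keeping two primaries is a legitimate alternative if the rule is written down (both required, or alpha split) and the power cost shown above is accepted.

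Cost: rewording only, with no extra patients or data. The downside is that the recovery endpoint loses co-primary status.

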#### Childhood Trauma Questionnaire (CTQ) (Bernstein et al., 2003)

Childhood trauma questionnaire is used to obtain measures of childhood trauma. This is a questionnaire inquiries about childhood maltreatment in five areas, hence severity of sexual, physical, and emotional abuse, as well as physical and emotional neglect. Each subscale has five items graded on a 5-point Likert scale (1 = never true, 5 = very often true). CTQ holds satisfactory psychometric properties across Norwegian samples (Dovran et al., 2013). To identify possible cases of trauma, we will also use this instrument to define accurate case determination with the recommended scoring options by Walker et al. (1999). Based on a receiver operating characteristic methods they determined threshold scores for each of the five subscales that provided very good to excellent sensitivity and specificity (≥0.85) for each of the five subscales. Patients who score ≥8 on the sexual abuse, physical abuse or physical neglect scale or ≥10 at emotional abuse scale or ≥15 at emotional neglect scale will be placed in the trauma group. The remaining patients, with scores below the thresholds for all five maltreatment groups, will be considered to be a non-trauma group. This last group contains patients with a range of maltreatment experiences from none to just below. In case of ambiguity regarding case determination, it will be resolved by consensus discussions with an experienced therapist independent of the study.

### Secondary Outcome Measurements

#### The Eating Disorder Examination-Questionnaire-6 (EDE-Q-6) (Fairburn et al., 1993)

Eating disorder examination-questionnaire is a self-report measure that was adapted from the interview-based EDE and measures ED pathology. The total score is used as an indicator for the level of ED pathology, with a higher score denoting more pathology.

#### Symptom Checklist-90-Revised (SCL-90) (Derogatis, 1983)

Symptom checklist-90-revised is a multidimensional patient-reported questionnaire for measuring psychological distress or the degree of affective distress. The global severity index (GSI), which is the global score covering all 90 items, will be used in the trial.

